#### Secondary outcomes

The secondary endpoints will include the following. Half an hour before drug administration, voriconazole plasma concentrations, and laboratory tests of participant were recorded; laboratory tests including C-reactive protein (CRP), procalcitonin (PCT), and erythrocyte sedimentation rate (ESR), etc. Meanwhile, adverse events and mortality at weeks 4 and 8 will also be recorded.

### Participant timeline {13}

The participant timeline is presented in Table 1.

**Table 1 Tab1:** The participant timeline

Viewpoint	V1	V2	V3	V4	V5	V6	V7	V8	V9	V10	V11
Time point	0 (baseline)	12 h	24 h	48 h	72 h	Week 1	Week 2	Week 3	Week 4	Week 6	Week 8
Use of voriconazole	Before treatment	Before the 2nd dose	Before the 3rd dose	Before the 5th dose	Before the 7th dose	Week 1	Week 2	Week 3	Week 4	Week 6	Week 8
Time-window	− 7	0	0	0	0	± 1	± 2	± 2	± 2	± 3	± 3
Informed consent	√										
Essential information	√										
Inclusion/exclusion criteria	√										
Previous treatments	√										
Previous medicine	√										
CYP2C19 gene	√										
Symptoms	√	√	√	√	√	√	√	√	√	√	√
Physical sign	√	√	√	√	√	√	√	√	√	√	√
Comorbidity	√	√	√	√	√	√	√	√	√	√	√
ECG	√										
Lung CT	√						√		√	√	√
Abdominal ultrasonography	√								√		√
Blood routine	√				√	√	√	√	√	√	√
Renal function	√								√		√
Inflammation indicators	√				√	√	√	√	√	√	√
G/GM test	√					√	√	√	√	√	√
BALF culture or histopathology	√										
Biochemical test	√				√	√	√	√	√	√	√
Coagulation function	√				√	√	√	√	√	√	√
ABG	√				√	√	√	√	√	√	√
Blood ammonia	√				√	√	√	√	√	√	√
Pregnancy test (female)	√										
Plasma voriconazole trough concentration		√	√	√	√	√	√	√	√	√	√
Concomitant medication	√	√	√	√	√	√	√	√	√	√	√
Child–Pugh classification	√					√	√	√	√	√	√
MELD score	√					√	√	√	√	√	√
Condition evaluation		√	√	√	√	√	√	√	√	√	√
AE	√	√	√	√	√	√	√	√	√	√	√
SAE		√	√	√	√	√	√	√	√	√	√

### Sample size {14}

We referred to a study about drug monitoring and safety of voriconazole therapy in patients with Child–Pugh B and C cirrhosis; this study suggested that about 30% of patients in group B (loading dose, 200 mg intravenously twice daily on day 1; maintenance dose: 100 mg intravenously twice daily) had voriconazole *C*_min_ > 5 mg/L on the third day of treatment [20].

Based on pharmacokinetic knowledge, we estimate that the rate of patients in the experimental group in this study with *C*_min_ > 5 mg/L after 3 days of treatment with voriconazole will not be lower than that in group B described above. The resulting sample size was calculated as follows:$${N}_{c}={\left({Z}_{1-\alpha /2}\sqrt{\overline{P }\left(1-\overline{P }\right)\left(1+r\right)/r} +{Z}_{1-\upbeta }\sqrt{{P}_{c}\left(1-{P}_{c}\right)+{P}_{T}\left(1-{P}_{\mathrm{T}}\right)/r}\right)}^{2}/{\left({P}_{c}-{P}_{T}\right)}^{2}$$

NC: control group sample size.

PC (control group rate): 0.6, PT (experimental group rate): 0.3,

$$\overline{P }$$ (mean of control group rate and experimental group rate): 0.45.

*r*: grouping ratio, *r* = 1 for 1:1 grouping.

*α*: type I error; *β*: type II error.

Here $$\alpha =0.05, \beta =0.1, Z1-\frac{\alpha }{2}=1.96, Z1-\beta =1.28$$

Substituting into the formula: NC ≈ 42.16. By grouping 1:1, then at least 43 cases were taken from each group. Considering 10% dropout, the study will require recruiting approximately 96 participants for all the groups (*n* = 48 in each group) to adequately test the assumption.

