**Methods:**

This study is a non-double-blind randomized controlled trial. The 96 eligible acute-on-chronic liver failure patients complicated with invasive pulmonary aspergillosis will be randomly assigned to receive either the optimized voriconazole regimen or the recommended voriconazole regimen for patients with mild to moderate liver cirrhosis (Child–Pugh A and B), at a 1:1 ratio, with an 8-week follow-up period. The antifungal efficacy of voriconazole will be the primary outcome measure. Plasma voriconazole trough concentration, the laboratory examination (CRP, PCT, ESR, etc.), chest CT, adverse events, and mortality at week 4 and 8 will be the secondary outcome measures.

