### Outcomes {12}

#### Primary outcome

The primary endpoint will be the antifungal efficacy of voriconazole. All patients treated with voriconazole were systematically evaluated by the same investigator on the team. Each patient was evaluated on the basis of case report, imaging (computed tomography scan, CT) findings. CT images of the lung were reviewed by two radiologists. Changes in lesions were assessed visually using computed planimetry to help estimate percentage change. The response categories for complete response, partial response, and treatment failure were the same as those in similar previous studies [16–19]. Complete responses were defined by the resolution of all clinical signs and symptoms and more than 90% of the lesions due to invasive aspergillosis that were visible on radiology. Partial responses were defined by clinical improvement and greater than 50% improvement in findings on radiology. Stable responses were defined by the absence of change from base line or an improvement of less than 50%. Failure of therapy encompassed progression and death due to IPA. Complete and partial responses were classified as successful outcomes.

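### The sample size is calculated for a day-3 trough proportion, so its stated 90% power does not apply to the primary endpoint, antifungal response

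*Protocol article*

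**What the plan says.** The Primary outcome section states: "The primary endpoint will be the antifungal efficacy of voriconazole". It grades response on clinical findings and CT, and fixes a binary success: "Complete and partial responses were classified as successful outcomes". The Methods paragraph of the abstract also makes antifungal efficacy primary and lists as secondary "Plasma voriconazole trough concentration, the laboratory examination (CRP, PCT, ESR, etc.), chest CT, adverse events, and mortality at week 4 and 8".

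The Sample size section contains the only calculation. It starts from a cited study in which about 30% of one dosing group had a trough above 5 mg/L on day 3. It carries that over to this trial with "we estimate that the rate of patients in the experimental group in this study with" such a trough, adding that this rate "after 3 days of treatment with voriconazole will not be lower than that in group B described above". The inputs are "PC (control group rate): 0.6, PT (experimental group rate): 0.3", with two-sided alpha 0.05 and beta 0.1. The result is 43 per group, raised to 48 per group (96 in total) for 10% dropout. The section says that this number is enough "to adequately test the assumption".

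The Trial design section calls the trial non-inferiority. The Statistical methods section compares rates by a chi-square test at P < 0.05.

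**The concern.** A reader who sees a 90% power calculation and a declared primary endpoint will take the first to describe the second. Here the calculation concerns over-exposure on day 3, and the endpoint concerns response of the infection. A 30-point reduction in the proportion over-exposed says nothing about how large a difference in response to expect, or how much loss of response would be tolerable.

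The practical risk lies in how the result is read. If response does not differ significantly in a trial labelled non-inferiority and described as adequately sized, the two regimens may be reported as equally effective when the data cannot rule out a large loss of efficacy. The Discussion section expects the findings to inform guidelines, so this matters beyond the trial.

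**Working it through.** **1. The plan's own figure.** The inputs, all from the Sample size section, are PC = 0.6, PT = 0.3, mean 0.45, r = 1, Z = 1.96 and 1.28.

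- First term: 1.96 × √(0.45 × 0.55 × 2) = 1.379
- Second term: 1.28 × √(0.6 × 0.4 + 0.3 × 0.7) = 0.859
- N = (1.379 + 0.859)² / 0.3² = 5.007 / 0.09 = 55.63

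The printed 42.16 is not reproduced. At 43 per arm, power for 0.6 v 0.3 is about 81%. This arithmetic slip is a separate defect, and the present point does not depend on it. The dropout step does reproduce: 43 / 0.9 = 47.8, so 48 per arm.

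**2. Which endpoint the inputs describe.**

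| Item | Sample size section | Primary endpoint |
|---|---|---|
| Measure | trough above 5 mg/L | complete or partial response |
| Time | after 3 days | CT-based, in an 8-week follow-up |
| Experimental rate | 0.3, from a cited study | none given |
| Control rate | 0.6, no source given | none given |
| Difference or margin | 0.3 | none given |

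The 0.6 is not explicitly labelled as a trough rate, but the context allows no other reading. No input belongs to the primary endpoint.

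**3. What 43 evaluable per arm could show for response.** The document gives no response rates, so those below are assumptions.

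*Superiority*, two-sided 5% chi-square test without continuity correction, power summed exactly over the two binomial distributions:

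| Assumed rates | Power |
|---|---|
| 25% v 40% | 32.7% |
| 40% v 55% | 27.8% |
| 50% v 65% | 30.0% |
| 30% v 50% | 49% |
| 30% v 60% | 81% |

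*Non-inferiority*, equal true rate p in both arms, one-sided 2.5%. The standard error is SE = √(2p(1 − p)/43), which is 0.0934 at p = 0.25 and 0.1078 at p = 0.50. Power is Φ(margin/SE − 1.96):

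| Assumed margin | p = 0.50 | p = 0.25 |
|---|---|---|
| 10 points | 15% | 19% |
| 15 points | 28% | 36% |
| 20 points | 46% | 57% |
| 25 points | 64% | 76% |

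Example at p = 0.50, margin 15 points: 0.15/0.1078 − 1.96 = −0.569, and Φ(−0.569) = 0.285.

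*Precision*: the 95% confidence interval half-width is 1.96 × SE, so 1.96 × 0.0934 = 18.3 points at p = 0.25 and 1.96 × 0.1078 = 21.1 points at p = 0.50.

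**4. If nobody drops out.** With 48 per arm the SE at p = 0.50 is √(0.5/48) = 0.1021, and the half-width is still 20.0 points. Power in all the 15-point scenarios stays at or below 40%.

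**The case against.** The strongest reply is that the size of any shortfall is conjecture. The document offers no response rate and no margin, so a 15-point effect is no better founded than a 30-point one. That stands. A reader might infer that the trial is badly underpowered for response whatever is assumed, and the document does not support this: at 30% v 60%, superiority power is 81%. Only the absence of any stated power is documentary; every figure beyond that is conditional.

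A reader might also infer that the sized measure is missing from the secondary outcomes. It is not. The Secondary outcomes section lists pre-dose plasma concentrations, and Table 1 schedules one at 72 h. Only the 5 mg/L cut-off is absent, and an analysis plan commonly settles such a detail.

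A trial may be sized on a secondary measure, and a separate analysis plan is announced. But the section neither says nor justifies that it does so, and a later plan does not alter a calculation already printed for another endpoint.

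Finally, one might infer that the sized measure ought to become primary. The document gives reasons for caution. Recruitment was to start in August 2021, before the protocol date of 30 November 2021, and the trial is open label, so a swap could look like outcome switching. It would also replace the stated efficacy question. Nor is the trough measure itself secure: the text makes 0.3 a floor for the experimental rate, and at 0.4 v 0.6 power with 43 per arm is about 46% (normal approximation).

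**Conclusion.** The point holds as an endpoint mismatch. The sample size and its 90% power are derived for the day-3 trough proportion, and the primary comparison of antifungal response has no stated power. This follows from the protocol text alone.

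Its size is conditional on assumed response rates and 43 evaluable patients per arm. Over the scenarios examined, superiority power runs from about 28% (15-point difference) to 81% (30-point difference). Non-inferiority power runs from about 15% (10-point margin) to 76% (25-point margin). An interval of roughly ±18 to ±21 points is the plainest summary of what the trial can say about response. The conflict between the non-inferiority label and the two-sided difference formula is related, but it is a separate matter and is not needed for this conclusion.

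**What to change.** Keep 96 patients and antifungal response as the primary endpoint, and amend the text as follows.

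- In the Sample size section, state that the calculation covers only the proportion with a trough above 5 mg/L after 3 days, and that the 90% figure is not the power for antifungal response.
- In the same section, print the power or the expected 95% confidence interval width for the response difference over a range of assumed rates, marked as assumptions.
- In the Statistical methods section, report response as a difference between arms with its 95% confidence interval, and state that a non-significant chi-square result will not be read as equal efficacy.

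This needs an amendment to the text but no further patients, visits or data. The downside is a less favourable stated figure for the primary endpoint.

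Making the 72 h trough proportion primary is an option for the sponsor to weigh, not the recommendation. It would need no new sampling, but it carries the costs of changing the primary endpoint of an open-label trial during recruitment and of giving up efficacy as the main question.

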## Introduction

### Background and rationale {6a}

Acute-on-chronic liver failure (ACLF) is a prevalent kind of liver failure in which patients acquire acute or subacute liver failure as a result of chronic liver disease [1]. Meanwhile, patients with acute-on-chronic liver failure are more susceptible to fungal infections, particularly the rising incidence of invasive pulmonary aspergillosis (IPA), which has been reported to be as high as 5.0–8.3% [2–4], with a significant increase in short-term mortality (73.5–100%) [2, 3, 5].

At present, amphotericin B, voriconazole, and echinocandins are three frequently prescribed drugs for IPA patients. Voriconazole is recommended as the first-line antifungal agent in the treatment of invasive aspergillosis in the guidelines of the Infectious Diseases Society of America in 2016 [6]. The routine intravenous dosing regimen for voriconazole is as follows: 6 mg per kilogram intravenously twice daily on day 1, then 4 mg per kilogram intravenously twice daily for at least 7 days, after which the patient may switch to oral voriconazole at 200 mg twice daily. The loading dose can make plasma trough concentration (*C*_min_) reach the steady-state concentration of voriconazole in the shortest time (24 h), and the final half-life of voriconazole is only 6 h, so it needs to be administered twice a day [7]. Its therapeutic effect and adverse reactions (such as hepatotoxicity, hallucination, mental abnormality, etc.) are closely related to plasma voriconazole trough concentration. Since voriconazole is mainly metabolized by the liver drug enzyme CYP450, liver injury caused by liver cirrhosis and liver failure may decrease the activity or number of metabolic enzymes, resulting in a decrease in voriconazole metabolism and a corresponding increase in the incidence of adverse reactions [7–10]. Voriconazole drug instructions indicate that for patients with mild to moderate liver cirrhosis (Child–Pugh A and B), the loading dose remains unchanged and the maintenance dose is halved. However, there is no recommendation for patients with severe liver cirrhosis (Child–Pugh C) and liver failure.

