### Intervention description {11a}

Eligible patients will be randomized to either the experimental group or the control group. According to the recent research on related topics and the previous retrospective studies of our research group, the experimental group will receive the optimized voriconazole regimen: first loading dose, 6 mg per kilogram intravenously; second loading dose (twelve hours interval from first dose), 2 mg per kilogram intravenously; maintenance dose, 2 mg per kilogram intravenously twice daily.

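### Sample size {14} claims 90% power for an unsourced 60% v 30% at day 3, although the arms appear to differ only in the 12 h dose; its printed formula also gives 56 per arm, not 43.

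*Protocol article*

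**What the plan says.** All references are to the protocol article.

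- **Sample size {14}** takes "PC (control group rate): 0.6, PT (experimental group rate): 0.3" for Cmin above 5 mg/L after 3 days. The 0.3 is borrowed from a group in a cited study of Child-Pugh B and C cirrhosis, and the text treats it as a floor for the experimental arm. The 0.6 has no source. With two-sided alpha 0.05 (z = 1.96), beta 0.1 (z = 1.28) and 1:1 allocation, the section reports "Substituting into the formula: NC ≈ 42.16", takes 43 per arm, and then: "Considering 10% dropout, the study will require recruiting approximately 96 participants for all the groups".
- **Intervention description {11a}** gives the experimental arm a first dose of 6 mg/kg, then "second loading dose (twelve hours interval from first dose), 2 mg per kilogram intravenously; maintenance dose, 2 mg per kilogram intravenously twice daily".
- **Explanation for the choice of comparators {6b}** makes the control the regimen recommended for Child-Pugh A or B cirrhosis, without listing doses. **Background and rationale {6a}** describes that regimen relative to routine dosing (6 mg/kg twice on day 1, then 4 mg/kg twice daily): "the loading dose remains unchanged and the maintenance dose is halved". The **Discussion** names the loading dose as the element that varies.
- **Participant timeline {13}, Table 1** samples troughs at 12, 24, 48 and 72 h. The 24 h sample is taken "Before the 3rd dose" and the 72 h sample before the 7th.

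**The concern.** On this reading the control arm receives 6, 6, 2, 2, ... mg/kg and the experimental arm 6, 2, 2, 2, ... mg/kg, every 12 h. The only difference is 4 mg/kg at 12 h. The sizing takes its contrast at the 72 h trough, 60 h and four identical doses later. A doubling of the exceedance rate at that point is a strong assumption, and nothing in the protocol supports it.

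If the true day-3 contrast is much smaller, the exposure comparison on which the trial is sized has little chance of success. A null result at 72 h could then be taken as no exposure difference, although the difference may lie mainly in the first 24-48 h, which the trial already samples.

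**Working it through.** **1. The plan's own figure.** Put the section's inputs into its formula (PC = 0.6, PT = 0.3, mean 0.45, r = 1):

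- 1.96 × √(0.45 × 0.55 × 2) = 1.96 × 0.7036 = 1.379
- 1.28 × √(0.6 × 0.4 + 0.3 × 0.7) = 1.28 × 0.6708 = 0.859
- N = (1.379 + 0.859)² / 0.3² = 5.007 / 0.09 = 55.6, so 56 per arm

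The printed 42.16 is not reproduced. It lies close to the 41.9 that z = 0.84 (80% power) gives. The dropout step is right: 43 / 0.9 = 47.8, so 48. From 56 it would give 62.2, so 63 per arm and 126 in total.

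Power = Φ[(|PC − PT|√n − 1.96√(2P̄(1 − P̄))) / √(PC(1 − PC) + PT(1 − PT))]. At 60% v 30%:

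- n = 43: (1.967 − 1.379) / 0.671 = 0.877, power 81%
- n = 48: (2.078 − 1.379) / 0.671 = 1.043, power 85%

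**2. Cap on the 72 h ratio.** Six doses precede the 72 h trough: 6+6+2+2+2+2 = 20 mg/kg (control) and 6+2+2+2+2+2 = 16 mg/kg (experimental). Let q be the fraction remaining after 12 h under linear elimination. Then

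ratio = 1 + 4q⁵ / [6q⁶ + 2(q + q² + q³ + q⁴ + q⁵)].

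This rises with q and reaches 1 + 4/16 = 1.25 at q = 1 (no elimination). The cap needs no half-life, only linear kinetics.

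**3. Ratio needed for 30% to 60%.** With lognormal troughs of log-SD s, the ratio needed is exp[s × (0.524 + 0.253)] = exp(0.778s): 1.26, 1.47 and 1.72 at s = 0.3, 0.5 and 0.7. A ratio of 1.25 suffices only if s ≤ ln(1.25) / 0.778 = 0.287.

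**4. Implied control rate and power.** Hold PT = 0.30 at 72 h, so PC = Φ(ln(ratio)/s − 0.524), and use 43 per arm. Half-lives and log-SDs are assumptions. Background {6a} gives 6 h in general and says it is prolonged in liver failure, without a figure.

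| Half-life | Ratio 24 h | Ratio 48 h | Ratio 72 h | PC; power, s = 0.3 | PC; power, s = 0.5 | PC; power, s = 0.7 |
|---|---|---|---|---|---|---|
| 6 h | 2.14 | 1.09 | 1.006 | 0.307; 2.9% | 0.304; 2.7% | 0.303; 2.7% |
| 12 h | 1.80 | 1.24 | 1.06 | 0.372; 10.5% | 0.343; 6.2% | 0.330; 4.9% |
| 24 h | 1.64 | 1.31 | 1.15 | 0.476; 38.7% | 0.403; 16.7% | 0.373; 10.5% |
| 48 h | 1.57 | 1.33 | 1.20 | 0.538; 61.1% | 0.439; 26.4% | 0.398; 15.5% |
| 72 h | 1.55 | 1.33 | 1.22 | 0.556; 67.5% | 0.450; 29.9% | 0.405; 17.3% |
| none eliminated | 1.50 | 1.33 | 1.25 | 0.587; 77.3% | 0.469; 36.1% | 0.419; 20.6% |

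**5. Settings that favour the plan.**

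- Linear kinetics, median half-life 72 h, log-SD 0.3 on half-life and 0.2 on level: control rate 62%, power 85%.
- Saturable elimination, assumed volume 2 L/kg, spread only in elimination capacity: control rates 59-88%. At 4.6 L/kg the experimental arm could not be brought to 30% above 5 mg/L, since 16 / 4.6 = 3.5 mg/L even without elimination.
- A separate saturable grid of 36 settings: the 72 h ratio exceeded 1.25 in 35 and was about 1.48 or more in roughly a quarter.

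**The case against.** **The control regimen is inferred.** No section of the article lists the control doses, the flow chart is not shown, and the retrospective cases in Background {6a} had a 400 mg loading dose with individualised maintenance. This stands as a caveat. Even so, the comparator section, the background and the Discussion all point the same way.

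**A reader might infer that the stated contrast cannot occur.** The documents do not support that. They state neither linear kinetics nor the variability, and step 5 shows assumptions under which about 60% is reached. The 1.25 cap is a result for linear kinetics, not a general bound.

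**A reader might infer that most of the contrast has gone by 72 h.** The share of the extra dose remaining is 2^(−60/half-life). It is 0.1% at 6 h and 18% at 24 h, but more than half once the half-life exceeds 60 h. With an unspecified prolonged half-life, this is not established.

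**A reader might infer that 24 h should replace 72 h as the sized comparison.** That does not follow either. Under the same linear model, 24 h power at 43 per arm is only 44-83% for half-lives of 48-120 h and log-SD 0.5-0.7. The only external rate in {14} is a third-day rate.

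**The harm may be limited.** Exceedance at 72 h is not the primary outcome, and earlier troughs are already taken. That lowers the stakes but does not justify the 0.6 or the 90%.

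**Conclusion.** The point holds in a limited form. The 0.6 is unsourced, and on the regimens as the article implies them it needs either very little between-patient spread with a long half-life, or strongly saturable elimination. The protocol invokes neither. Under linear kinetics with half-lives of 12-72 h and log-SD 0.5-0.7, power at 43 per arm is about 5-30%. At log-SD 0.3 it is at most 77%, even with no elimination. These figures rest on the inferred control regimen, PT = 0.30, lognormal troughs and the assumed ranges.

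The arithmetic fault depends on none of this. By the section's own formula and z values, 90% power needs 56 per arm. The planned numbers give 81% (43) to 85% (48) even if 60% v 30% is true.

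**What to change.** Leave the regimens and the 96 patients as they are. In Sample size {14}:

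1. Replace PC = 0.6 with a rate derived from the actual dose difference between the arms, by a cited source or a pharmacokinetic simulation.
2. State the half-life, the type of kinetics and the between-patient variability assumed.
3. Correct the arithmetic and restate the power at 72 h for the planned numbers.
4. Prespecify the between-arm comparison of Cmin above 5 mg/L at the 24 h and 48 h troughs alongside 72 h, so that a null at 72 h is not read as no exposure difference.

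The cost is wording and a short calculation. No new samples or patients are needed, because Table 1 already includes these troughs. The downsides are a less favourable stated power and a few more secondary comparisons.

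### The printed sample-size formula gives 56 per group, not 43, so the planned size has about 81 to 85% power for the trough-concentration comparison, not the stated 90%

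*Protocol article*

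**What the plan says.** Sample size {14} starts from a cited study of patients with Child–Pugh B and C cirrhosis, in which about 30% of one dosing group had a trough above 5 mg/L on the third day. It expects that the experimental rate in this trial "will not be lower than that in group B described above".

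It then prints a two-proportion sample-size formula with these inputs:

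- the rates: "PC (control group rate): 0.6, PT (experimental group rate): 0.3";
- the "mean of control group rate and experimental group rate): 0.45";
- the allocation ratio r: "1 for 1:1 grouping";
- alpha 0.05 with Z 1.96, and beta 0.1 with Z 1.28.

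The result is given as: "Substituting into the formula: NC ≈ 42.16. By grouping 1:1, then at least 43 cases were taken from each group". A 10% dropout allowance raises this to 48 per group and 96 in all, which the section says is enough to test the assumption adequately. The abstract repeats the total: "The 96 eligible acute-on-chronic liver failure patients complicated with invasive pulmonary aspergillosis".

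**The concern.** Formula, inputs and result stand together in one section, so the result can be checked directly, and it does not follow from the inputs. The step is not harmless, because every later number (43, 48, 96) is built on it.

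At stake is the power the protocol claims. Beta 0.1 tells readers and the ethics committee that a difference of 60% v 30% would be missed one time in ten. If the planned size gives a larger type II error, a non-significant result on this comparison would be read with more confidence than the design supports.

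**Working it through.** **Inputs**, all from Sample size {14}: PC = 0.6, PT = 0.3, mean 0.45, r = 1, Z = 1.96 (alpha 0.05, two-sided), Z = 1.28 (beta 0.1).

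**1. The printed formula with the printed inputs.** With r = 1,

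NC = [1.96·√(2·0.45·0.55) + 1.28·√(0.6·0.4 + 0.3·0.7)]² / (0.6 − 0.3)²

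- First term: 1.96·√0.495 = 1.3790
- Second term: 1.28·√0.45 = 0.8587
- NC = (1.3790 + 0.8587)² / 0.09 = 55.63, so 56 per group

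Unrounded Z values give 55.68, again 56. The plan's 42.16 is not reproduced.

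**2. Does another formula give 42.16?** Keeping two-sided alpha 0.05 and 90% power:

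| Variant | Per group |
|---|---|
| Unpooled variance | 52.5 |
| Pooled variance in both terms | 57.8 |
| Arcsine | 55.9 |
| Continuity-corrected | 62.2 |

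None is close. Two variants that depart from the printed inputs do come near: the same formula at 80% power (41.97, or 41.92 with Z = 0.84), and an unpooled formula with one-sided alpha 0.05 and 90% power (42.8). Solving the printed formula for 42.16 gives Z = (0.3·√42.16 − 1.3790)/0.6708 = 0.848, which is 80.2% power.

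**3. Dropout step.** 43/0.9 = 47.8, so 48 per group and 96 in total. This step is correct; the fault lies only in the substitution.

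**4. Power at the planned size.** For 60% v 30%, two-sided 5%, power = Φ[(0.3·√n − 1.3790)/0.6708]:

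| Evaluable per group | Formula | Exact enumeration, uncorrected chi-square |
|---|---|---|
| 43 | 81.0% | 81.0% |
| 48 | 85.1% | 85.4% |
| 56 | 90.2% | 89.6% |

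The type II error is therefore about 0.19 with 43 evaluable and about 0.15 with 48, against the stated 0.10.

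**5. What 90% would need.** 56/0.9 = 62.2, so 63 per group and 126 in total, 30 more than planned.

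**6. Sensitivity to PT, with PC held at 0.6.** With 43 per group, the same formula gives 64.5% power at PT = 0.35 (exact 64.0%) and 45.7% at PT = 0.40 (exact 44.8%). The values 0.35 and 0.40 are illustrative assumptions, not figures from the protocol.

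**The case against.** The error in the substitution cannot be argued away, but four points limit what follows from it.

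*The endpoint.* A reader might infer that the trial as a whole has 81% power. The document does not support that. The calculation is for the trough above 5 mg/L, and trough concentration is a secondary outcome (Abstract, Methods; Outcomes {12}). The primary outcome is antifungal response, and Trial design {8} calls the trial non-inferiority. The 81% does not apply to the primary comparison. This objection stands.

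*The floor on PT.* Because the text says the experimental rate will be no lower than 30%, a reader might infer that 0.30 is the most favourable case. That holds only if PC stays at 0.6, and the section gives no source for 0.6. Background and rationale {6a} reports that all four retrospective patients exceeded the safe range on the loading dose recommended for Child–Pugh A and B. Four cases with individualised maintenance doses prove little, but they give no reason to treat 0.6 as a ceiling. With 43 per group, 65% v 35% gives 81% power, 70% v 35% gives 92%, and 70% v 40% gives 81% (the PC values are assumptions). Taking the edge of an expected range as the planning value is an assumption, not an arithmetic error. This objection stands too, and the main point does not need the floor.

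*Dropout.* The 81% supposes the full 10% loss. The trough is read at about 72 hours (Table 1), so loss by then may be smaller. Hence the range of 81 to 85%; its upper end is still below 90%.

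*80% power is often accepted.* That may be so, and 42.16 lies close to the 80% result. But the document states beta 0.1 and does not say that another value was used, so this remains a guess about how the figure arose.

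**Conclusion.** The printed inputs give 55.63, so 56 per group, and the stated 42.16 is wrong as written. For the proportion with a trough above 5 mg/L after 3 days, at 60% v 30% and two-sided 5%, the planned size gives about 81% power with 43 evaluable per group and about 85% with 48, not 90%.

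The arithmetic rests on nothing outside the section. The power figures rest on the protocol's own rates, of which 60% is unsourced. They say nothing about power for antifungal response or for a non-inferiority conclusion. The document does not settle whether the slip is in NC or in beta and its Z value, so the sponsor has to reconcile them. The results for PT above 0.30 are secondary and hold only with PC fixed at 0.6.

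**What to change.** Keep 96 patients and make Sample size {14} agree with itself in one of two ways:

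- keep beta 0.1 and Z 1.28, correct NC to 55.6 (56 per group) as the 90% requirement, and say that the planned enrolment does not meet it; or
- drop beta 0.1 and Z 1.28, and restate the design power as about 81% with 43 evaluable per group, rising to about 85% with 48.

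In either case, name the endpoint (trough above 5 mg/L after 3 days), say that the figure is not the power for antifungal response, and amend the minimum of 43 per group and the closing claim of adequacy. Correcting NC alone would leave a need for 56 per group beside an enrolment of 48. Changing beta to 0.2 alone would not do either: with Z = 0.84 the formula gives 41.92, still not 42.16.

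Optionally, add one sentence of sensitivity, explicitly conditional on PC = 0.6: about 64% power at PT = 0.35 and about 45% at PT = 0.40, with 43 per group. It should not call 0.30 the most favourable case without that condition.

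The cost is a wording correction, with no extra patients and no change to conduct. The downside is that the stated power becomes less favourable.
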